**Principal investigator (MMC No. if applicable): [name] and [name] [name] (MMC: 43103)**

**Co-researchers: (MMC No. if applicable): [name] [name] (UTM)**

**Introduction**

Alcohol is a common and easily accessible addictive substance. There are a large number of drinkers worldwide, and the impact of alcohol-related problems cannot be ignored. According to the latest Global Status Report on Alcohol and Health 2018 released by the World Health Organization (WHO) [1], there are about 2.3 billion drinkers in the world at present. In 2016 alone, about 3 million deaths could be attributed to the harmful use of alcohol, accounting for 5.3% of the total number of deaths, while drinking was also responsible for 132.6 million disability-adjusted life years (DALYs). Alcohol consumption is related to more than 60 kinds of diseases and injuries, mainly involving cancer, cardiovascular diseases, digestive diseases, traffic accidents and intentional injuries, etc. It is the third pathogenic risk factor after hypertension and smoking [2]. With the development of economy, the production and consumption of alcoholic beverages increased rapidly. According to the report of WHO [1], the per capita alcohol consumption in China soared from 4.1 liters in 2005 to 7.2 liters in 2016, while the lifelong abstinence rate decreased from 50.9% in 2005 to 42.1% in 2016. The prevalence of alcohol use disorder (AUD) in China is also increasing year by year. At present, the prevalence of AUD is 6.9% in males and 0.2% in females [3]. Alcohol-related problems have become one of the important public health problems in China, and the situation is quite serious.

**Problem statement & Study rationale**

AD is a chronic and recurrent mental disorder. It will affect the brain's ability to control emotions, decisions and behaviors, resulting in the decline of work and learning abilities, impaired physical and mental health, and even legal problems. AD poses a serious threat to individual health, family well-being and social stability. Therefore, how to effectively treat the disease and prevent relapse is of great significance. So far, many studies on alcohol addiction have not been able to fully elucidate its pathogenesis, which is generally considered to be caused by neurobiological, psychological and sociological factors [4]. Previous studies have suggested that the most important neuroadaptive changes in the progression from occasional drinking to addiction may be down-regulation of the dopamine (DA) and gamma aminobutyric acid (GABA) systems, as well as permanent up-regulation of the glutamate (Glu) system, in addition to disruption of the brain's stress system: Dysregulation of corticotropin releasing hormone (CRH) and serotonin (5-HT) [5]. Other studies have found that alcohol sensitivity is closely related to addiction, and prolonged alcohol intake can reduce the body's response to alcohol, which is one of the risk factors leading to AD [6].

In addition, studies on the mechanism of addiction tend to be based on the theory of "reward system", which mainly involves the mesolimbic dopamine system [7] and endogenous opioid system [8]. Studies on psychological and sociological factors consider that alcohol addiction is related to psychological reinforcement, personality traits, alcohol accessibility, family environment, peer influence and social cultural background, etc. [9-11].

The core symptoms of AD mainly include two aspects: one is physical dependence based on increased alcohol tolerance and withdrawal reaction, and the other is psychological dependence based on alcohol craving [4]. Currently, clinical treatment for AD is focused on reducing physical dependence. Benzodiazepines (BZD) are usually given to alleviate withdrawal symptoms, low-dose antipsychotics to relieve psychotic symptoms, and adequate vitamin B supplementation to prevent Wernicke encephalopathy. However, most patients still have a strong craving for alcohol during abstinence, even after receiving standardized in-patient treatment. This psychological dependence on alcohol is hard to resist, so it is extremely difficult to maintain long-term abstinence, and AD is prone to relapse. Therefore, psychological dependence is the key factor leading to alcoholics drinking again after abstinence, and the monitoring and treatment of alcohol craving is an important link to improve the therapeutic effect of AD.

Existing studies on the treatment of AD have found that the effect of drug therapy on alcohol craving is very limited. The US Food and Drug Administration (FDA) has approved three drugs for abstinence: disulfiram, naltrexone and acamprosate. As a kind of alcohol sensitizer, disulfiram causes patients to appear strong physical discomfort after ingesting a small amount of alcohol, which has a high risk and cannot effectively reduce craving, so it is basically no longer used clinically.

In view of the high relapse rate and rising prevalence of AD, it is of great significance to find new methods that can effectively intervene in alcohol craving, which should be easy to be popularized and applied in clinical practice. New therapies should integrate biological, psychosocial and environmental factors in order to improve the abstinence rate and reduce the relapse rate. It will provide a breakthrough in the treatment for AD and even the field of addiction medicine.

The treatment and detection methods adopted in this study include probiotics treatment, intestinal microflora detection, ERP detection, and multi-parameter physiological index detection. All of the above are emerging technologies, tools and research hotspots in recent years, and all of them have the advantages of safety, and non-invasive.

Probiotics therapy is a simple, safe and low-cost treatment method, which can restore intestinal flora homeostasis, repair intestinal barrier, improve nutritional status and other physical conditions of patients to a certain extent. It is expected to regulate patients' mood, reduce patients' craving for alcohol and reduce the recurrence rate through the gut-brain axis. Intestinal flora detection can also monitor the changes of patients' flora, evaluate the therapeutic effect of probiotics, and hopefully analyze the main flora affecting the enteric-brain axis in AD patients, providing a theoretical basis for further research.

ERP detection has excellent time resolution and can objectively evaluate the psychological activities of patients. The application of this technology has the advantages of high efficiency, economy, high sensitivity and non-invasive to subjects. In addition, combined with EEG traceability analysis, it can study the characteristics of alcohol craving. The combination of these emerging therapeutic methods and detection methods in this study will help break through the bottleneck of AD treatment and prevention at the present stage, optimize the treatment plan, improve the quality of life of AD patients, reduce the social burden, and produce obvious social and economic benefits.

**Research Question(s)**

1. Does probiotic or ACT result in significant improvement in biological markers, and reduce the degree of AD symptoms severity among patients diagnosed with alcohol dependence after 8 weeks of intervention?

2. Does probiotic or ACT result in significant improvement in rate of alcohol repetition and alcohol withdrawal symptoms and degree of craving?

3. Whether ACT treatment or probiotics can cause EEG changes in alcohol dependent patients?

**Objective**

**Primary objective:**

To determine the differences in the severity of alcohol dependence, alcohol withdrawal and craving among patients on Lactobacillus sp., placebo and ACT, at 4 timelines (baseline, 8 weeks after starting intervention, 12 weeks after starting intervention, and 24 weeks after starting intervention which is 12 weeks post termination of intervention).

**Secondary objectives:**

(1) To determine the differences in the serum levels of pro-inflammatory cytokines among patients on Lactobacillus sp., placebo and ACT, at 4 timelines (baseline, 8 weeks after starting intervention, 12 weeks after starting intervention, and 24 weeks after starting intervention which is 12 weeks post termination of intervention).

(2) To assess the differences in severity of depression and anxiety symptoms among patients on Lactobacillus sp., placebo and ACT via use of questionnaire, at 4 timelines (baseline, 8 weeks after starting intervention, 12 weeks after starting intervention, and 24 weeks after starting intervention which is 12 weeks post termination of intervention).

(3) To investigate the changes of EEG characteristics in patients with AD after the above related treatments, at 3 timelines (baseline, 2 weeks after starting intervention, 8 weeks after starting intervention).

(4) To assess the differences in gut microbiota profiles of patients on Lactobacillus sp., placebo and ACT via the use of fecal samples, at 3 timelines (baseline, 2 weeks after starting intervention, and 8 weeks after starting intervention).

**Literature review**

**2.1 Relationship between intestinal flora and alcohol dependence**

Over the past decade, the link between the gut, and specifically the gut microbiome, and alcohol dependence has come to the attention of researchers. In individuals with alcohol addiction, drinking can disrupt intestinal barrier function, also known as intestinal leakage[12-13]. The intestinal barrier consists of intestinal cells, goblet cells, and antibacterial substances that influence the intestinal microbiota within the mucus layer, as well as many immune cells in the lamina propria[14]. The mechanism by which alcohol or its metabolites cause intestinal leakage is unknown, and may be related to intestinal disorders, immune system activation, and inflammation. Dysbiosis of intestinal flora refers to changes in intestinal flora, which is characterized by changes in intestinal bacterial groups, such as decreased levels of anti-inflammatory bacteria and increased abundance of Proteus[15-16]. Animal studies have shown that improved intestinal barrier integrity can ameliorate alcohol-induced liver injury[17-19]. This suggests that treatment modulated by the gut microbiome, such as probiotics, may be beneficial for patients with AD. Persistent alcohol abuse can change fecal pH, promote excessive growth of pathogens, and alter the function of intestinal microorganisms by altering the secretion of specific metabolites involved in intestinal barrier dysfunction [20-21]. Elevated levels of plasma cytokines such as TNF α , interleukin and CRP in PATIENTS with AD suggest chronic, low-grade, systemic inflammation[22]. In the past decade, several studies have suggested a link between systemic inflammation and psychiatric disorders such as alcohol addiction, depression, and autism, and the gut microbiome could be a good target for research. One possible mechanism of systemic inflammation and alcohol addiction is that intestinal bacterial products activate peripheral blood monocytes and induce cytokines to enter the blood, leading to alcohol addiction and other psychiatric disorders, including major depressive disorder, bipolar disorder and anxiety disorder[23]. The severity of alcohol addiction is related to the intensity of patients' cravings, cognitive dysfunction, anxiety and depressive symptoms.

Thus, systemic inflammation may play an important role in the development of alcohol addiction, but causality remains unclear. However, alcohol cravings and negative emotions such as anxiety and depression were highly associated with alcohol-seeking behavior and relapse, suggesting that reducing systemic inflammation may improve mental health and prevent relapse. Probiotics are healthy microbes, and alcohol dependent patients had fewer bifidobacteria and lactobacillus in their gut than the normal population. Oral supplementation of good bacteria can help restore gut flora and improve alcohol-related illness. In ethanol-fed rats, lactobacillus GG supplementation can reduce endotoxemia and alcohol-induced liver injury[24]. In alcohol-dependent patients, supplementation of Bifidobacterim bifidum and Lactobacillus plantarum 8PA3 during alcohol detoxification had a greater effect on the reduction of liver enzymes than dietary restriction alone[25]. In patients with alcoholic cirrhosis, administration of lactobacillus casei Shirota improved neutrophil phagocytosis compared with conventional treatment[26]. In addition, in patients with alcohol use disorders, administration of VSL#3(a mixture of eight different strains), Compared with traditional treatment, plasma levels of TNF α , IL-6 and IL-10 were significantly reduced[27]. These data suggest that probiotics have beneficial effects on the enteric-liver axis in alcohol-dependent patients. Several clinical trials have demonstrated beneficial effects of probiotics on psychological symptoms and brain activity[28]. On the gut-brain axis, intake of prebiotics and probiotics was beneficial for neurochemical changes in rats, including increased hippocampal expression of brain-derived neurotrophic factor and glutamate receptors[29], which are involved in the regulation of many behaviors, such as anxiety, depression, cognitive performance, and addiction[30]. Recent research suggests that gut bacteria may influence brain function and behavior. As demonstrated by Temko et al., alcohol dependence, other substance use disorders and eating disorders are all associated with changes in neurobiological pathways in specific regions of the brain involved in "reward" processing[31], and changes in gut flora may alter biological pathways by reducing systemic inflammation. However, Sophie Leclercq et al. showed in their review that the effects of intestinal flora on the neurobiological processes of patients with substance use disorder still need to be further studied, and probiotics or prebiotics are a promising treatment method for alcohol dependence and substance dependence.

**2.2 Acceptance and commitment therapy (ACT)**

ACT is a third generation therapy, which is new from cognitive behavioral therapy (CBT), and it is approach to produce psychological flexibility. Psychological flexibility is defined as the ability to contact the present moment more fully as a conscious human being and to change or persist in behavior when doing so serves valued ends [32]. Unlike CBT, which aims to change unhelpful thoughts and feelings. ACT was designed to increase adaptive coping through acceptance, cognitive defusion, mindfulness, and perspective-taking exercises while supporting clients in aligning behavior with their personal values [33-34]. ACT facilitates development and maintenance of health behavioral improvements by targeting internal barriers [35]. ACT can be used to treat depression and anxiety by teaching patients the right way to deal with negative emotions and relieve psychological symptoms.The alcohol-seeking behavior of AD patients is often associated with anxiety and depression. It may be possible to reduce the frequency of alcohol-seeking behavior by alleviating bad mood.Therefore, the use of ACT in the treatment of AD patients is a worthwhile approach.

**2.3 Research Progress of Event-related Potential Technology**

Event-related potential (ERP) is a special evoked EEG. When the body receives multiple or diverse events with psychological significance, there will be a "time-locked" relationship between the EEG and the stimulation, which can reflect the neural electrophysiological phenomenon of the brain in the process of cognitive processing. ERP is an "online window" to observe the mental activities of human brain, which can make objective evaluation of advanced mental activities[36]. In the past, many scholars have used ERP technology to carry out studies on substance addiction, especially in the composition of ERP-P300. P300 is associated with a variety of cognitive processes and is an indicator of a variety of neurocognitive processes, including attention and working memory. Some studies suggest that abnormal ERP amplitude may be a disease marker of substance dependence and a potential neurobiological endophenotype[37]. Bartholow et al. used an experimental paradigm containing images with alcohol cues to detect P300, and found that the P300 response of subjects with low sensitivity to alcohol was significantly enhanced, while that of subjects with high sensitivity to alcohol was not.

Moreover, such enhanced P300 response was alcohol-specific and would not be extended to other motivational related stimuli. Alcohol cue-induced P300 may be a sensitive endophenotype for the risk of alcohol addiction[38]. Petit et al. 's study showed that alcoholics had enhanced ERP responsiveness to alcohol-related cues, especially male patients[39]. Meta-analysis on drug dependence indicated that in the detection of attention preference and craving in drug cue images, the increase of cue-induced P300 amplitude was correlated with the increase of subjects' craving degree[40]. The previous study of our research team[41] found that there were positive results in EEG analysis of AD patients in the craving state induced by static pictures of alcohol cues, that is, AD patients presented lower N200 amplitude and higher P300 amplitude under the stimulation of alcohol cues, which were positively correlated with the subjective craving scale score. It is possible to objectively assess the psychological dependence of AD patients by using alcohol cue response to induce the craving for alcohol and monitoring the task-state EEG (ERP) of the subjects at the same time.

In conclusion, drinking alcohol can change the intestinal barrier and intestinal flora of AD patients. Changes in intestinal flora have a certain degree of influence on AD patients, but the specific mechanism remains to be further studied and clarified. Regulation of gut microbiota through the use of probiotics or prebiotics is a promising and safe treatment for AD. Prospective randomized controlled clinical trials are still needed to evaluate the effects of probiotics and/or prebiotics on AD, especially on the different behavioral manifestations of AD. Such as studying the effects of probiotics and/or prebiotics on depression, anxiety, stress response, cognition, impulsivity, and alcohol-seeking behavior in patients with AD. In addition, ERP is an economical, non-invasive and objective method to reflect the psychological dependence of AD patients. ERP testing in conjunction with studies of probiotics and/or probiotics in the treatment of alcohol-dependent patients may help to better evaluate and reveal the specific impact of intestinal flora on patients with AD.

**Conceptual framework**

[figure not shown]

**Research design**

A double-blind randomized controlled trial design has been chosen.

**Study area**

The study will be completed in the Second Affiliated Hospital of Xinxiang Medical University, Xinxiang, Henan, China.

**Study population**

In this study, patients with alcohol dependence who met the diagnostic criteria of "alcohol use disorder" in DSM-5 were selected as the experimental group. Advertisement with posters will be placed on display in the 2nd Affiliated Hospital of XXMU and the Department of Psychiatry, XXMU to help in the recruitment of subjects. Healthy people who met WHO healthy drinking standards or did not drink were used as the healthy control group. The experimental group was divided into probiotics + routine treatment group and placebo + routine treatment group and ACT + routine treatment group.

**Subject criteria**

A) The AD subjects

a) Inclusion criteria:

-Hospitalized patients diagnosed with untreated alcohol use disorder (confirmed by the diagnostic criteria of DSM-5).

-Male, age 18 to 55 years old, Han nationality, junior high school education or above,

right-handed.

-Those with normal eyesight, including corrected vision(screened clinically).

b) Exclusion criteria:

-The patient suffer from other mental illnesses (screen by DSM-V criteria).

-The patient has allergy reaction to medications use for conventional treatment of alcohol use disorder.

-The patient had a history of organic brain disease, a pacemaker, gastrointestinal surgery, or serious health problems.

-The patient had a history of seizures.

-The patient is complicated with severe physical disease.

-Patient has other drug dependence (except for nicotine dependence).

-The patient took drugs affecting intestinal flora 30 days before and during admission.

-The patient has participated in any other alcohol-related studies or trials within the past

30 days.

-Patients had use any prescription or over-the-counter drugs in the past 30 days that may

affect mood or alcohol cravings.

B）Healthy control group

a) Inclusion criteria:

-Male, age 18 to 55 years old, Han nationality, junior high school education or above,

right-handed.

-No history of psychoactive substance abuse, except tobacco (screen with urine dipstick test).

-Those with normal eyesight, including corrected vision (screen clinically).

-No alcoholic beverages in the last 2 weeks.

-According to the WHO healthy alcohol consumption standard, the average intake of

pure alcohol per week is less than 210 grams, or do not drink at all (screen clinically).

b) Exclusion criteria:

-Those who suffer from other mental illnesses (screen by DSM-V criteria).

-Those who has history of organic brain disease, a pacemaker, gastrointestinal surgery, or serious health problems.

-Those who has history of seizures.

-Those complicated with severe physical disease.

-Those with drug dependence, including alcohol dependence (exception for nicotine dependence).

-Those who took drugs affecting intestinal flora 30 days before and during admission.

-Those who has participated in any other alcohol-related studies or trials within the past

30 days.

-Those who use any prescription or over-the-counter drugs in the past 30 days that may

affect mood or alcohol cravings.

**Sample size estimation**

A total number of 108 patients are needed, with n=36 per arm inclusive of a possible 20% dropout (total n=90; n=30 per arm, without dropout). The sample size was calculated for a parallel group study design involving three arms and was based on power design analysis. This is a higher number required for the primary outcome of AD, and types of interventions as described below. All these calculations were based on the need for a continuous response variable from independent control and experimental subjects, with a ratio of control to subject fixed at 1:1, power of 0.80 and Type-I error probability associated with this test of null hypothesis of 0.05.

Based on the use of ACT for reducing alcohol craving in patients with alcohol use disorder (AUD) and comorbid affective disorder, a sample size of 21 patients per arm is needed, comprising of 26 patients per arm including an additional 20% dropout. The administration of ACT showed decreased OCDS score with a standard deviation of 4.6 within group was observed, accompanied by decreased score of 4.0 between ACT and control groups[42].

Based on the use of probiotics for reducing alcohol dependence syptom in AD patients, a sample size of 30 patients per arm is needed, comprising of 36 patients per arm including an additional 20% dropout. The administration of probiotics showed decreased HAMD score with a standard deviation of 19.25 within group was observed, accompanied by decreased score of 17.75 between probiotics and control groups[43]. Hence, the estimated number of healthy subjects needed for initial comparison with AD subjects was also at 108 subjects.

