**Study flowchart**

**Figure 3.1. Flow chart of the study**

**Data analysis**

All data analysis will be performed using SPSS software version 25.0 (SPSS Inc, Chicago, IL, USA). Descriptive statistics for socio-demographic and clinical characteristics, CIWA-Ar, PACS, AUDIT, VAS, HAMD, and HAMA scores, ERP analysis, and serum pro-inflammatory cytokine levels will be computed. All categorical variables will be presented in frequency and percentage, while all continuous variables will be reported in mean and standard deviation or median and interquartile range, depends on normality. Differences in socio-demographic and clinical characteristics between the three groups will be computed with Pearson’s chi square test or one way ANOVA or Kruskal Wallis test.

The mean difference in the primary outcome (CIWA-Ar, PACS, AUDIT, and VAS scores) for the three randomized groups (ACT, probiotic, and palcebo groups) at each specific time point (pre-intervention, 2 weeks at completion of conventional treatment [t0], post-treatment at 8 weeks [t1], post-treatment at 12 weeks [t2], and post-treatment at 24 weeks [t3]) will be assessed using one way analysis of variance (ANOVA) followed by false discovery rate adjustment. For the main pool analysis, mixed ANOVA is used to determine the interaction between the groups (ACT, probiotic, and placebo groups) and time points (t0, t1, t2, and t3) on the primary outcome ( CIWA-Ar, PACS, AUDIT, and VAS scores; interaction = intervention × time; where time is a within-subject variable and intervention effect is a between-subject variable). The main effects of intervention in the groups and time points will be presented as estimated marginal mean and standard error of mean. The study’s primary analysis will follow the intention-to-treat (ITT) principle. The data analysis for the study’s secondary outcomes (severity of anxiety and depressive symptoms, pro-inflammatory cytokines, EEG characteristics, and fecal microbiota) will be conducted similarly to the primary outcomes’ calculation. Statistical significance will be two-tailed and set to p < 0.05.

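### The 30 evaluable patients per arm that set the trial size do not follow from their stated inputs, and 36 per arm less 20% dropout does not leave 30

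*Protocol*

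**What the plan says.** All sizing figures are in the Protocol, Sample size estimation. The headline is "A total number of 108 patients are needed, with n=36 per arm inclusive of a possible 20% dropout", and the same sentence gives 90 in total and 30 per arm as the numbers without dropout. The calculations are for a "continuous response variable from independent control and experimental subjects", "with a ratio of control to subject fixed at 1:1", with "power of 0.80 and Type-I error probability associated with this test of null hypothesis of 0.05". The Data analysis section adds that "Statistical significance will be two-tailed and set to p < 0.05".

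Two calculations follow:

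- **ACT:** OCDS difference 4.0, SD 4.6. The conclusion is "a sample size of 21 patients per arm is needed, comprising of 26 patients per arm including an additional 20% dropout".
- **Probiotic:** HAMD difference 17.75, SD 19.25. The conclusion is "a sample size of 30 patients per arm is needed, comprising of 36 patients per arm including an additional 20% dropout".

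The section adopts the larger requirement, the probiotic one. It then carries 108 over to the number of healthy comparison subjects.

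**The concern.** The probiotic calculation prints every input needed to check it, and its standardised difference (0.922) is larger than that of the ACT calculation (0.870). A larger standardised difference at the same alpha and power needs fewer patients, yet the plan reports more: 30 against 21. So the 30, or one of its inputs, is misreported.

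The dropout step is a separate fault. The plan presents 36 as already allowing for 20% loss and 30 as what remains, but 20% of 36 is 7.2.

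At stake is whether a reader can reproduce the planned size. The 30 fixes 36 per arm, 108 patients and, by extension, 108 healthy subjects. On the printed inputs the probiotic requirement is not the larger of the two, so the stated reason for choosing 108 does not hold.

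**Working it through.** **Inputs.** From Sample size estimation: power 0.80, alpha 0.05, 1:1 ratio, two independent groups, dropout 20%, and the differences and SDs above. From Data analysis: two-sided testing.

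**Formula.** Normal approximation, per arm: n = 2 (z₀.₉₇₅ + z₀.₈₀)² / d², where d = difference/SD and (1.960 + 0.842)² = 7.849. The exact two-sample t-test is the cross-check.

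**Step 1. ACT figure.** d = 4.0/4.6 = 0.870. n = 2 × 7.849 / 0.756 = 20.8, so 21 (t-test 21.8, so 22). The stated 21 reproduces, which also shows that the formula fits the plan's own approach.

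**Step 2. Probiotic figure.** d = 17.75/19.25 = 0.922. n = 2 × 7.849 / 0.850 = 18.5, so 19 (t-test 19.5, so 20). The stated 30 does not reproduce.

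**Step 3. Could another reading give 30?** Probiotic inputs, per arm:

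| Variant | n per arm (normal / t-test) |
|---|---|
| One-sided alpha 0.05, power 0.80 | 15 / 16 |
| Two-sided alpha 0.025, power 0.80 | 23 / 24 |
| Two-sided alpha 0.05/3, power 0.80 | 25 / 27 |
| Two-sided alpha 0.05, power 0.90 | 25 / 26 |
| Three-group ANOVA F-test, alpha 0.05, power 0.80 | about 16 to 24, by pattern of means |
| Two-sided alpha 0.01, power 0.80 | 28 / 30 |
| Two-sided alpha 0.05/3, power 0.85 | 28 / 30 |
| Two-sided alpha 0.025, power 0.90 | 30 / 31 |
| Two-sided alpha 0.05, power 0.95 | 31 / 32 |

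Only the last four come near 30, and each uses an alpha or power that the Protocol does not state.

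**Step 4. What 30 per arm means.** With d = 0.922, power at 30 per arm is 0.940 (t-test) or 0.946 (normal). With SD 19.25 and power 0.80, 30 per arm corresponds to d = 0.736, a difference of 0.736 × 19.25 = 14.2.

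**Step 5. Dropout.**

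- 36 × 0.80 = 28.8 per arm; 108 × 0.80 = 86.4 in total. The plan states 30 and 90.
- 36 = 30 × 1.20. That covers a loss of 6/36 = 16.7%, not 20%.
- For 30 to remain: 30/0.80 = 37.5, so 38 per arm and 3 × 38 = 114 in total.
- ACT: 21/0.80 = 26.25, so 27 against the stated 26.

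**Step 6. Power after dropout on the printed inputs, at 28 per arm.** HAMD effect: 0.923 (t-test), 0.932 (normal). OCDS effect: 0.892 (t-test), 0.902 (normal).

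**Step 7. Power after dropout if 30 is the true requirement for 80%.** With d = 0.736, t-test power is 0.771 at 28 per arm and 0.783 at 28.8.

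**The case against.** The strongest reply is that nothing is lost. On the printed inputs 30 exceeds the 19 to 20 required, and even after dropout both sizing effects keep more than the planned 80% power. That stands, and it limits the weight of the point. A reader might infer that the trial is underpowered, and the Protocol's figures do not support that.

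On dropout, adding 20% to 30 does give 36, and the shortcut is common. The gap is only 30 − 28.8 = 1.2 expected completers per arm. The primary analysis is by intention to treat and multiple imputation is foreseen, so patients who leave need not vanish from the analysis, although they cost information. All this makes the shortfall small. It does not make the headline sentence true, because that sentence calls 20% the dropout and 30 the number left.

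The ACT figures are also less faulty than they look. The 21 reproduces and should stay. The 26 does not by itself prove the wrong inflation: 21 × 1.2 = 25.2 rounds up to 26, and 26.25 rounds to 26 as well. The correction is one patient.

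Finally, one cannot simply write 20 in place of 30. The Protocol does not show whether the 30 or one of its inputs is wrong. For the same reason, a reader might infer that the trial enrols too many patients and could be cut to the ACT requirement. That takes the printed inputs as correct, and it rests on scales that are not the primary outcomes.

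**Conclusion.** The point holds as a reporting error in figures the trial relies on. The governing 30 per arm is about 50% above what its inputs give (19 to 20), and the evaluable number is overstated by 1 to 2 patients per arm (about 86 in total against 90).

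The consequence depends on which entry is wrong:

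- **Inputs right, 30 wrong:** the error is conservative. Power after dropout is about 92–93% for the HAMD effect and 89–90% for the OCDS effect.
- **30 right, an input wrong:** about 28 to 29 evaluable per arm gives roughly 77–78% power, slightly under the stated 80%.

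These results assume pairwise two-sided comparisons of means at alpha 0.05, as the Protocol describes, and the loss of exactly 20% of patients. A reader might take the percentages as the power of the trial. They are not: the primary outcomes in Data analysis are CIWA-Ar, PACS, AUDIT and VAS, tested by a mixed-ANOVA interaction, whereas HAMD is secondary and OCDS is not among the planned questionnaires.

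**What to change.** Keep 108 randomised and restate the Sample size estimation section:

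1. Reconcile the probiotic requirement with its inputs. Either correct it to 19 (normal formula) or 20 (t-test), or state the difference, SD, power or alpha that gives 30. Only the sponsor can tell which applies.
2. Give the expected evaluable number at 20% dropout as about 28 to 29 per arm, about 86 in total.
3. Inflate for dropout by n/(1 − 0.20) throughout. The ACT 21 stays and becomes 27; a retained 30 would need 38 per arm.
4. Give the power at the evaluable number for the reconciled inputs. Label it as applying to the HAMD and OCDS effects and not to the primary mixed-ANOVA outcomes.
5. Restate why 108 was chosen, for patients and for healthy subjects, if the probiotic requirement is no longer the larger one.

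The cost is protocol wording only. No patients are added and no analysis changes. The stated evaluable number becomes slightly less favourable.
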